#### Exclusion Criteria

Participants with any of the following will be excluded: anemia (hemoglobin level <7%); hypertension; diabetes mellitus; hepatic or renal disease; cardiac disease; organic lesions of the reproductive tract due to conditions such as tuberculosis, carcinoma, and congenital deformities; pelvic inflammatory disease or cervicitis; evidence of malignancy, cervical intraepithelial neoplasia, or cervical carcinoma; history of untreated sexually transmitted disease or being HIV positive; past history of atrial fibrillation, acute coronary syndrome, myocardial infarction, stroke, or severe arrhythmia in the last 6 months; lactating women; current or previous use of oral contraceptive pills, glucocorticoids, antiandrogens, ovulation induction agents, antidiabetic drugs, antiobesity drugs, or other hormonal drugs recently (unless there is a washout period of 1 month); hypersensitivity to the trial drugs or any of their ingredients; currently participating in any other clinical trial or participated in past 6 months; or any other condition that the principal investigator thinks may jeopardize the study.

### Study Interventions (Investigational Products)

Participants in the treatment group will receive 250 mg of *Trinakantamani*
*pishti* twice a day orally before meals, 20 mL of *Ashokarishta* twice a day orally before meals, and 1 iron and folic acid tablet (100 mg of elemental iron and 1.5 mg of folic acid) twice a day orally after meals for 3 months. The treatment group’s medicines (investigational products) will be procured from Good Manufacturing Practices–certified pharmacies, namely, Indian Medicines Pharmaceutical Corporation Ltd. and Central Ayurveda Research Institute, along with the Certificate of Analysis to ensure the quality and safety of the medicines. The study drugs will be kept in a secure place and will only be supplied to the participants under the guidance of the investigator. A record will be maintained for the drug dispensed. Any discrepancies between amounts dispensed and returned will be explained.

Participants in the control group will receive a 500-mg tranexamic acid tablet thrice a day for 7 days from the first day of menses for 3 cycles and 1 iron and folic acid tablet twice a day orally for 3 months.

### Strategies to Improve Adherence to Study Protocol

The compliance of taking trial drugs will be assessed at each visit during the follow-ups (30-day intervals) by assessing the approximate quantity consumed. The participants will be asked to return the empty container of medicine at the time of each follow-up visit. Repeated reminders will be given over the phone or through family members and project staff for regular taking of medicine.

### Outcome Measures

#### Primary Outcome Measures

Primary outcome measures are changes in the amount of uterine bleeding evaluated by the PBAC, changes in the duration of bleeding, and the attainment of a normal amount of blood loss during the interval of cycles, evaluated at baseline, the end of every cycle up to 3 cycles, and follow-up visits.

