### Eligibility Criteria

#### Inclusion Criteria

Participants will include those aged 20-50 years with menorrhagia—that is, regular (21-35 days) cycle with HMB loss, subjectively or objectively defined (Pictorial Blood Assessment Chart [PBAC] score of more than 100 points) [12], or prolonged bleeding (bleeding more than >7 days) for 3 consecutive cycles—who are willing and able to participate in the study.

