### Sample Size

To calculate the sample size, we anticipated a difference of 70 units in average PBAC score after treatment between the two groups (*Trinakantamani*
*pishti* along with *Ashokarishta* vs tranexamic acid tablet), with an SD of 137 units based on the results of the previous study [14]. With 95% confidence level (α=.05) and 80% power, the number of patients to be enrolled in the study was calculated using the following formula:

where *Z*_1 – α/2_=1.96, *Z*_1 – β_=0.84, σ=137, and δ=70.

Expecting a dropout rate of 15%, the number of patients is estimated to be 60 + 9 = 69. Thus, approximately 70 patients should be enrolled in each group.

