### Statistical Methods

Continuous variables will be presented as mean, SDs, medians, and ranges. Categorical variables will be summarized with frequencies and percentages. When inferential analyses will be conducted for continuous variables, they will be tested for normality. Nonparametric methods will be used to compare nonnormal data. Within-group comparison will be done using a paired *t* test (1- or 2-tailed, as suitable), while between-group comparisons will be done using an independent sample *t* test (1- or 2-tailed, as suitable) for the data following normal distribution. Nonnormal data within the group will be compared using the Wilcoxon sign rank test, while between groups comparison will be done by using the Mann-Whitney *U* test. Categorical data between groups will be compared using the chi-square or Fisher exact test. A 2-sided *P* value of <.05 will be considered statistically significant. Per-protocol and intention-to-treat analyses will be carried out at the end of the study. All data will be analyzed using Stata (version 16.1; Stata Corp).

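### Three unranked primary outcomes with no deciding time point or success rule, in a trial sized for one PBAC comparison: either the 5% level or the 80% power is not secured

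*Protocol article*

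**What the plan says.** Four parts of the protocol article bear on this point.

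- **Primary Outcome Measures.** "Primary outcome measures are changes in the amount of uterine bleeding evaluated by the PBAC, changes in the duration of bleeding", followed by "the attainment of a normal amount of blood loss during the interval of cycles". These are "evaluated at baseline, the end of every cycle up to 3 cycles, and follow-up visits". The abstract lists the same three. Neither place ranks them, names a deciding time point, or says how many must succeed.
- **Study schedule (Table 2).** PBAC is assessed at baseline and at five later visits (days 30, 60, 90, 120 and 150). The table has no separate row for duration or for attainment of normal loss.
- **Statistical Methods.** "A 2-sided *P* value of <.05 will be considered statistically significant". The section describes pairwise tests chosen by data type, with no order among the primaries. It also leaves the direction of the tests open: "between-group comparisons will be done using an independent sample *t* test (1- or 2-tailed, as suitable").
- **Sample Size.** "we anticipated a difference of 70 units in average PBAC score after treatment between the two groups", with an SD of 137, alpha .05 and 80% power. This is one outcome and one comparison.

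**The concern.** The sample-size section treats the trial as having one primary test, whereas the outcome section declares three, each read several times. The two sections cannot both describe the trial's main claim.

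What is at stake depends on a rule that the document does not give. If one favourable result out of three is enough, the claim of efficacy carries more than a 5% risk of being false. If all three are needed, the 80% power was never calculated for that requirement. With no deciding time either, the choice of what to headline stays open until results are visible. The open choice of one- or two-tailed tests, beside a two-sided threshold, adds to that freedom.

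**Working it through.** **Step 1: reproduce the plan's own figure.** Inputs from Sample Size: difference 70, SD 137, Z values 1.96 and 0.84. With the usual formula for two means:

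n per group = 2 × [137 × (1.96 + 0.84) / 70]² = 2 × (5.48)² = 60.06

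This matches the stated 60 per group. With unrounded Z values and rounding up, the result is 61. A one-sided test would need 48, so the sizing is two-sided at .05. Power with 60 evaluable per group is 79.9%. The figure is correct for one comparison and has no allowance for a second or third primary.

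**Step 2: any one success counts, one time point.** Three tests at .05, all nulls true.

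- Independent: 1 − 0.95³ = 0.143.
- Correlated: simulated with equicorrelated normal statistics and a cut-off of |z| > 1.96. The documents give no correlations, so these are assumed.

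| Assumed correlation between outcomes | Chance of at least one false positive |
|---|---|
| 0 | 14.3% |
| 0.5 | 12.6% |
| 0.7 | 10.9% |
| 0.8 | 9.8% |
| 0.9 | 8.4% |

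**Step 3: any one success counts, and every time point is also tested.** The document does not announce this, so it is a worst-case scenario.

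- Three outcomes × three cycle ends = 9 tests. Independent: 1 − 0.95⁹ = 0.370. With assumed correlations of 0 to 0.9 between outcomes and 0.5 to 0.8 between times: about 16% to 33%.
- Three outcomes × five post-baseline visits = 15 tests. Independent: 1 − 0.95¹⁵ = 0.537. With the same assumed correlations: about 20% to 45%. With one common correlation of 0.9 across all 15 tests: about 14%.

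**Step 4: all three must succeed at one fixed time.** The false-positive rate does not exceed 5%. Joint power cannot exceed the power of the PBAC test alone (79.9% at 60 per group). It equals that only if the other two are significant whenever PBAC is. For illustration, if each outcome had 80% power and they were independent, joint power would be 0.80³ = 51%. The document gives no effect size for duration or attainment, so the actual figure cannot be computed.

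**Step 5: cost of keeping three primaries with an alpha split.** With Bonferroni, each is tested at .05 / 3 = .0167. The PBAC comparison then needs 81 evaluable per group, or 81 / 0.85 = 95.3, rounded up to 96 enrolled per group at 15% dropout. At 60 evaluable per group, PBAC power falls from 79.9% to 65.7%.

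**The case against.** The strongest reply has four parts.

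**The success rule is unstated, so inflation is not established.** This stands. A reader might infer that the trial's false-positive rate is simply well above 5%. The document supports that only if any single success counts. Under an all-must-succeed rule the level holds and the loss is in power. What can be said without assumption is that the plan secures one or the other, but not both.

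**The large figures assume testing that is not announced.** This also stands. A reader might take 54% as the trial's error rate. But the outcomes are described as evaluated at each cycle and visit, not as tested there. Table 2 schedules only PBAC by name. Independence is also implausible for three measures of the same menses. The 15-test figures mark an upper bound and are not an estimate.

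**Multiplicity handling may be in an unseen analysis plan.** This stands in part. Adjustment methods and models for repeated measurements may well be there, and their absence from the article is not the point. Which outcome is primary, and when it is read, is a protocol decision. The article makes that decision by naming three with no deciding time, then sizes on one.

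**Attainment of normal loss.** A reader might infer that some women already meet this outcome at entry whatever their treatment. Women can indeed enter without a PBAC score above 100, since heaviness may be "subjectively or objectively defined (Pictorial Blood Assessment Chart [PBAC] score of more than 100 points") and prolonged bleeding is an alternative route. But the document never defines normal loss as a PBAC of 100 or less, and the Introduction describes normal and heavy loss in mL. A woman starting at or below 100 could also exceed it later. Such women would be expected in both randomised arms, where they would dilute a difference but not raise the false-positive rate. This is a separate matter of definition.

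**Conclusion.** The point holds. Three unranked primaries, several reading times, no success rule, one 5% threshold and a sample size for one PBAC comparison are inconsistent as a set. If any success counts, the false-positive rate at a single time is about 8% to 14% over assumed correlations from 0.9 to 0, and higher if cycles or visits are also tested. If all must succeed, the 5% level is kept but the stated 80% power is unsupported. The facts about the text are certain. The rates are conditional on the success rule and on correlations that the documents do not give.

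It would go too far to say that the sample-size section already fixes the third menses as its endpoint. It refers only to PBAC after treatment.

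**What to change.** Before any comparative data are seen, amend the protocol and registry wording as follows.

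1. Name one primary endpoint: the between-group comparison of PBAC at one prespecified end-of-treatment assessment, tested at two-sided .05. The third treated cycle is one possible choice. It is consistent with the sample-size section but not stated there. Timing needs care. With 21 to 35 day cycles and a first menses between day 0 and day 35, the third menses could start anywhere from day 0 + 42 = 42 to day 35 + 70 = 105. State also whether PBAC is analysed as a change, as the outcome section says, or as a post-treatment score, as the sample-size section says.
2. Make duration of bleeding and attainment of normal loss key secondary endpoints, tested in fixed order and only if PBAC is significant.
3. Treat all other time points as supportive.
4. Separately, define normal loss. If the PBAC cut-off of 100 is used, analyse attainment among women whose baseline PBAC is above 100.

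The cost is wording only. Alpha stays at .05 and the planned sample size is unchanged. The downside is that duration and attainment lose stand-alone primary status. Keeping all three as primaries with a Bonferroni split would instead need 81 evaluable per group for PBAC.

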### Study Procedure

The participants will be screened for menorrhagia as per the inclusion criteria. Prior to any trial-related activity, the investigator will give the verbal information and written information in a printed form about the trial to the participant, parents, or guardians to read and understand. The investigator would ensure that the participants are fully informed about the aims, procedures, discomforts, and expected benefits of the trial. It must be emphasized that participation is voluntary, and participants have the right to discontinue the trial at any time without any prejudice. A voluntary, signed informed consent will be obtained from the participants prior to any clinical trial–related procedure.

After the screening, if the participants are found to be suitable, then they shall be enrolled in the study after signing the consent form. The required investigations will be carried out, and subsequently, within one week or as soon as laboratory values are received and found to be within permissible limits, the participants will be enrolled in the study, and that day will be considered visit 1 or the baseline visit. The treatment will be given to the participants after fulfilling all the formalities as per the protocol. The subsequent follow-ups will be on the 30th day (visit 2), the 60th day (visit 3), the 90th day (visit 4), the 120th day (visit 5), and the 150th day (visit 6; ie, completion of active treatment). Participants will visit the study site 6 times during the trial. The details of the activity during each visit are presented in Table 2 and Figure 1.

**Table 2 table2:** Study schedule.

Components	Screening	Baseline (visit 1)	30th day (visit 2)	60th day (visit 3)	90th day (visit 4)	120th day (visit 5)	150th day (visit 6)
Informed consent	✓						
Demographics and medical history		✓					
Laboratory investigations	✓		✓		✓		
Assessment of clinical signs and symptoms		✓	✓	✓	✓	✓	✓
Assessment of the MIQ^a^		✓	✓	✓	✓	✓	✓
Clinical examination	✓						
Assessment of the PBAC^b^		✓	✓	✓	✓	✓	✓
Assessment of ADRs^c^			✓	✓	✓		
Assessment of drug compliance			✓	✓	✓		
Issue of trial drugs every 20 or 30 days							

^a^MIQ: Menorrhagia Impact Questionnaire.

^b^PBAC: Pictorial Blood Loss Assessment Chart.

^c^ADR: adverse drug reaction.

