### Data Collection, Management, and Analysis

The data collection will include all information in the CRFs. All participants will be assigned an enrollment number, which will be used on CRFs and electronic databases. Consent forms and CRFs will be stored in locked cupboards, and electronic databases will be password protected. The data will be entered using the double-entry method for accuracy. All data will be accessible to the principal investigator and coinvestigators during and after the study has been completed and will be available to sponsors and monitors as required. Data will be stored for 5 years before being destroyed. In case of dropout, 10% data will be inserted through the imputation technique. Proper documentation will be done to ensure its accurate interpretation and verification. The analysis will be done by the Central Council for Research in Ayurvedic Sciences statistical unit.

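### No primary visit is fixed for PBAC, and the named between-group tests leave out its baseline; one baseline-adjusted contrast would settle both

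*Protocol article*

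**What the plan says.** Primary Outcome Measures lists three primary outcomes: "changes in the amount of uterine bleeding evaluated by the PBAC, changes in the duration of bleeding, and the attainment of a normal amount" (the last refers to menstrual loss). All three are "evaluated at baseline, the end of every cycle up to 3 cycles, and follow-up visits". Table 2 in Study Procedure ticks PBAC at baseline and at days 30, 60, 90, 120 and 150, so there are five post-baseline assessments.

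Statistical Methods chooses tests by data type. For normally distributed data it specifies a two-sample t test: "between-group comparisons will be done using an independent sample". For other data, "between groups comparison will be done by using the Mann-Whitney *U* test". Paired t and Wilcoxon tests are named for changes within a group. The significance threshold is a two-sided P below .05. Intention-to-treat and per-protocol analyses are both planned. No baseline covariate is mentioned.

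Sample Size rests on one between-group difference of 70 PBAC units after treatment, with SD 137, and does not say at which visit. On missing data, Data Collection, Management, and Analysis says: "In case of dropout, 10% data will be inserted through the imputation technique".

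**The concern.** The article fixes the assessment times, the tests and the threshold, but together these do not define one primary PBAC result. A comparison after treatment could be read as day 90, which Laboratory Tests calls the end of treatment. It could be day 150, which Study Procedure describes as the completion of active treatment, or it could be an average over cycles. Those two descriptions need to be reconciled in any case. The trial is open-label, and its limitations section says that the investigators knew the allocation, so a visit left open until analysis weakens the primary result.

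The second issue is efficiency. The outcome is defined as change and every woman has a baseline PBAC, yet the between-group tests do not adjust for it. Whether a t test on post-treatment scores or on change scores does better depends on a correlation that the article does not give.

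**Working it through.** **Inputs from the article.** Difference 70, SD 137, Z values 1.96 and 0.84, 70 women per arm, 15% dropout (Sample Size); three treated cycles and five post-baseline visits (Primary Outcome Measures, Table 2).

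**Assumed, because the article gives no value.** Correlation between test statistics at different visits: 0.4 to 0.8. Correlation between baseline and later PBAC: 0.3, 0.5 or 0.6, equal for all pairs of visits. SD 137 at every visit.

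**1. The plan's own figure.** n = 2 × (137 × (1.96 + 0.84) / 70)² = 2 × 5.48² = 60.06. The stated 60 per group is reproduced. It is the size for one two-sample comparison of post-treatment PBAC.

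**2. Several tests at .05.** Chance of at least one P<.05 when there is no effect, by simulation of equally correlated normal test statistics (1,000,000 draws):

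| Correlation | 3 cycles | 5 visits |
|---|---|---|
| 0.4 | 13% | 20% |
| 0.6 | 12% | 17% |
| 0.8 | 10% | 13% |

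**3. Baseline adjustment at one visit.** Completers per arm: 70 × 0.85 = 59.5. For post-treatment scores, SE = 137 × √(2/59.5) = 25.12, and power = Φ(70/25.12 − 1.96) = Φ(0.83) = 79.6%. Analysis of covariance (ANCOVA) multiplies the SE by √(1 − ρ²); a change-score test multiplies it by √(2(1 − ρ)).

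| ρ | Post-treatment scores | Change score | ANCOVA |
|---|---|---|---|
| 0.3 | 79.6% | 65% (SE 29.72) | 83.2% (SE 23.96) |
| 0.5 | 79.6% | 80% (SE 25.12) | 89.6% (SE 21.75) |
| 0.6 | 79.6% | 88% (SE 22.47) | 93.6% (SE 20.09) |

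The 95% CI half-width (1.96 × SE) is 49.2 units for post-treatment scores and 47.0, 42.6 or 39.4 for ANCOVA.

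**4. What the other cycles add.** A repeated-measures model was evaluated by generalised least squares with a common baseline mean and 5% of women lost before each of cycles 1, 2 and 3. It gives cycle-3 power of 83.5%, 90.0% or 94.0%. Over ANCOVA on completers that is 83.5 − 83.2 = 0.3, 90.0 − 89.6 = 0.4 and 94.0 − 93.6 = 0.4 percentage points. The half-widths are 46.8, 42.3 and 39.0 units. Almost all of the gain comes from the baseline.

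**The case against.** The strongest objection is that the article nowhere commits to a test at every visit. It lists tests by type of data, and the sample size points to one contrast. This stands: the error rates in step 2 describe what the wording allows, not what is planned.

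A reader might also infer that women who leave early are discarded. The article does not support this, since it plans imputation for dropouts and an intention-to-treat analysis. What can be said is narrower. The imputation sentence names no method, and its 10% matches neither the 15% dropout in Sample Size nor the 20% in the Abstract.

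A third tempting reading is that the power gain shows repeated data being wasted. Step 4 shows otherwise, because the repeated-measures part is worth only 0.3 to 0.4 points.

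Nor are two-sample tests the only ones named, since paired tests are too, although those do not compare the arms. A two-sample test at one named visit is valid under randomisation, and details such as covariance structure belong in a statistical analysis plan, which may exist. Adjusting for baseline is therefore an improvement in precision, not the correction of an invalid test. The open visit is different: the article states the times and the threshold itself, and as stated they do not identify one primary PBAC result.

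**Conclusion.** The point holds in a limited form. PBAC has five post-baseline assessments and no primary visit, so the text permits several tests at .05. If all were run, the false-positive chance would be about 10-13% over three cycles or 13-20% over five visits, under the assumed correlations. Separately, the between-group comparison leaves out a baseline that is already collected. Adjusting for it is worth roughly 4 to 14 percentage points of power over the post-treatment test (83.2 − 79.6 = 3.6; 93.6 − 79.6 = 14.0). ANCOVA also beats the change-score test at all three assumed correlations, so the sponsor need not know the correlation in advance.

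The power figures assume SD 137 at each visit, a difference of 70 at the chosen visit, 15% dropout and approximate normality. None of them shows that the stated sample size is wrong, as 60 per group is reproduced.

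**What to change.** In Primary Outcome Measures and Statistical Methods, name one primary PBAC contrast, for example the between-arm difference at the end of cycle 3. Estimate it with a 95% CI from a model on all randomised women that includes baseline PBAC. Either ANCOVA at that visit or a repeated-measures model on all observed cycles would serve. The second adds little power, but it uses women with partial data under a missing-at-random assumption and avoids relying on the unclear imputation sentence for this outcome. Label the other visits supportive. Keep a rank-based sensitivity analysis, because PBAC may be skewed and the article already provides for non-normal data. Name the primary visit for the other two primary outcomes as well, since they share the same assessment times.

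The cost is a change of wording and a standard Stata command, with no extra visits, patients or data. The downside is slightly more modelling and no freedom to choose the visit afterwards. Enrolment stood at 79 of 140 in December 2024 and analysis is due by February 2026, so the change should be recorded before any between-group outcome data are examined.
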